### Intervention

The GPs will delegate to the practice nurses the tasks of risk assessment, patient education and counselling. The practice nurses will be equipped to roll out an intervention comprising (1) risk assessment, (2) risk communication, (3) distribution of a decision aid and (4) motivational interviewing. These strategies will be distributed over two consultations and a follow-up telephone call (see Figure 2). Each consultation will take about 15 minutes, with a maximum of 30 minutes. The duration of the phone call will vary, but is not meant to last over 10 minutes.

**Figure 2 F2:**
[figure not shown]
**Graphical depiction of intervention and measurements**. Graphical depiction of intervention and measurements (above), with legend (below). Squares represent fixed elements, e.g. objects and calculations. Circles represent activities that are flexible. Randomisation and measurements are shown in grey. This graphical method was proposed by Perera et al [76].

#### (1) Risk assessment

The assessment of the 10-year risk of CVD will be done with the help of the risk table from the Dutch guideline on CVRM, published and produced in 2006 by the Dutch Institute for Health Care Improvement (CBO), in close collaboration with the Dutch College of General Practitioners (NHG), and has also been approved by the relevant clinical specialist groups, such as cardiologists [6,46]. The risk table is derived form the European Score risk table [46], adapted to the Dutch situation. The cardiovascular risk of patients with diabetes will be estimated with a table derived from the UKPDS risk engine [47].

#### (2) Graphical risk communication tool

The risk communication tool is a sheet showing graphical information that the nurse can use to communicate the risk more explicitly to the patient. It has been suggested that risks can be more understood by patients if different ways are used to present them, such as natural frequencies, positive and negative framing and a population chart. It has also been recommended to explain the uncertainty to the patient [48]. The practice nurse can visualise the total risk, as well as the relative contributions of modifiable risk factors to the total risk. Both absolute and relative risks will be framed and depicted in numbers (by natural frequencies) and in graphs (by population diagram). The risk communication tool was developed in a pilot study. A practice nurse from a general practice that will not be included in the main study administered the tool to 8 patients, who were interviewed about the different graphical risk presentations, clarity, language and layout of the tool. The tool was then adapted on the basis of the outcomes of these interviews.

#### (3) Decision aid

An earlier version of the decision aid was tested in an RCT by [name] [45]. The 16-page decision aid (in brochure form) informs patients about their absolute 10-year CVD risk, both verbally and numerically, and presents options for risk reduction, such as use of medication or lifestyle changes. The risk table from the guideline on CVRM is also made available to the patients. The brochure will be handed over by the nurse to the patient at the end of the first consultation. The patient is expected to read the decision aid at home and return to the nurse to discuss what should or should not be done.

#### (4) Adapted Motivational Interviewing

In the second consultation, the nurse will apply adapted motivational interviewing to support the patient in the process of decision making about CVRM. The first step is to set the agenda for the consultation, together with the patient [36]. The patient will chose one or more key items in CVRM (smoking, physical exercise, dietary behaviour, alcohol consumption and adherence to medical treatment) in this agenda setting. After this, the nurse will assess the patient's current behaviour and motivation for change, by rating and exploring importance and confidence with respect to the chosen key items. If there is a need and sufficient motivation for change regarding one or more items, the nurse will consult with the patient to select one item as the goal for behaviour change. The nurse will inform the patient about local opportunities for individual or group support in lifestyle change that tie in with the patient's goal, if appropriate.

##### Follow-up

Little is known about the number of consultations featuring motivational interviewing that is needed to optimise the effect in terms of behaviour change, as regards intensity and frequency but the assumption is that a second motivational interviewing consultation will probably increase the effect of the intervention [49]. Therefore, the nurse will apply the same adapted motivational interviewing in the follow-up telephone call (lasting a maximum of 10 minutes). The nurse will assess the patient's actual motivations for change, ask for their experiences with specific actions (if applicable) and continue to work on importance and confidence.

The intervention can be embedded in a long-term treatment approach. After the telephone consultation, the nurse and the patient decide whether and what continuation is needed, for example some extra consultations to support the lifestyle change or regular monitoring of weight or blood pressure.

##### Training

The nurses will receive a two-day training, outside the practice. The GPs will only be invited for the part of the training that concerns the new guideline on CVRM. Homework about risk assessment and motivational interviewing will be sent to the nurses with the request to study the materials, which should take them about 4 hours. The two-day training consists of the following elements:

- Introduction 1: hour

- Outlining the multifaceted strategy and various aspects of the study: 1 hour

- Information on the new guidelines for CVRM, on the assessment of the individual 10-year risk of CVD by means of vignettes, on the recommendations for lifestyle counselling and risk reduction by medication such as blood pressure or cholesterol lowering drugs: 1.5 hours.

- Communicating the risk to patients using a risk communication tool, and disseminating the decision aid to patients: 2 hours.

- Specific training in the adapted motivational interviewing technique that is to be used to discuss the decision aid with patients after it has been studied by them at home; involving patients in decision making and goal setting: 7 hours.

Afterwards:

- After completing the training course, the nurses will audiotape 3 consultations and will receive written feedback from the researchers on their communication techniques.

### Usual care

The practice nurses for the control group will receive only a short training on the new guideline for CVRM and will be instructed to administer usual care consistent with current guidelines. Usual care depends on patients' risk profile and their preferences for risk reduction. In normal situations, when blood pressure and cholesterol levels are sufficiently controlled, the guidelines recommend one follow-up consultation a year. In order to keep the nurses in the control arm motivated, the extended training in risk communication and motivational interviewing will be offered after the inclusion period of the trial and after the short-term measurement at 12 weeks. To protect the contrast between the intervention group and the control group, the nurses for the control group have to 'promise' not to administer the intervention to the included patients before their last measurement (52 weeks). The nurses will receive a list of the included patients in their practice, specifying the exact moment of the last measurement for each patient.

#### Effect evaluation

The aim of the effect evaluation is to examine the patients' adherence to lifestyle advice. The research question is: *What is the effect of a nurse-led intervention for CVRM, including risk communication, a decision aid and adapted motivational interviewing, on patients' adherence to lifestyle advice?*

### Variables and measurements

Primary outcome measures are the patients' adherence to lifestyle advice and drug treatment. The current state-of-the-art in measurement of adherence behaviour is a multi-method approach that combines feasible self-reporting and reasonably objective measures [50,13]. Specific behaviours relating to smoking, saturated fat intake, fruit and vegetable consumption, physical exercise, alcohol use and use of cardiovascular medication will be reported by patients, using validated self-reported questionnaires. For a detailed overview of the outcome measures, questionnaires and types of variables, see Tables 1 and 2. We will use pedometers at 12 weeks to measure physical exercise [51], although we recognise that this measurement may itself increase activity levels. Pedometers are reasonably accurate for walking activities [50]. Patients will be instructed to measure during 3 days in one week [52]. Body mass index will be measured as a proxy measure of healthy diet and exercise.

**Table 1 T1:** Primary outcome measures

**Outcome measure**	**Instrument **(Number of items, reference, validated yes/no)	**Analysis**
Fruit and Vegetables	8 items; [66]; Validated questionnaire	mean sum score; proportion meeting recommendations
Fat intake	35 items; [67] Validated questionnaire	mean sum score
Physical exercise	15 items; [68, 69]; validated questionnaire, modified Dutch version of the CHAMPS has not been validated.	mean; proportion meeting recommendations
Smoking	2 items; [70]; Validated questionnaire	proportion smoking
Alcohol consumption	2 items; [71]; validated questionnaire	proportion meeting recommendations
Adherence to medical treatment	5 items; (MARS) [72], not validated	mean
Cholesterol level	[6] Measured by nurse	mean score, proportion above recommendation
Blood pressure	[6] Measured by nurse	mean score, proportion above recommendation
Body Mass Index	[6] Measured by nurse	mean score, proportion above recommendation
10-year risk of CVD	based on patient's sex, age, blood pressure, cholesterol and smoking behaviour; [73];	mean score, proportion above recommendation

**Table 2 T2:** Secondary outcome measures

**Outcome measure**	**Instrument **(Number of items, reference, validated yes/no)	**Analysis**
Perception of own health behavior	1 item for each primary lifestyle outcome; question with 5-point scale	mean
Attitude towards behaviour change	1 item for each primary lifestyle outcome; question with 5-point scale	mean
Self-efficacy about specific behaviour change	1 item for each primary lifestyle; question with 5-point scale	mean
Risk perception	2 items; [74]	mean
Anxiety	2 items; [45]	proportion
Satisfaction with communication and confidence in decision	20 items; (COMRADE) [75]	mean

Clinical endpoints will not be assessed, but the absolute risk of cardiovascular events in 10 years will be calculated using the risk table from the Dutch guideline for CVRM [6]. For patients with diabetes, the UK PDS risk engine will be used. Calculation of the patients' absolute risk of cardiovascular events in 10 years, which is a proxy measure of actual health gain, will be based on known and available determinants: diabetes, age, sex, smoking, blood cholesterol level and systolic blood pressure. After one year, the risk of CVD will also be estimated, by deriving data on the risk factors from medical records in general practice. Since there is (according to the CVRM guidelines) no need to assess someone's cholesterol level annually if this level is acceptable, it is possible that some of the data used for the estimation will not be recent (with a maximum of one year).

Secondary outcome measures are the perception of the patients' own health behaviour, risk perception, anxiety, self-efficacy, importance of behaviour change, satisfaction with communication and confidence in the decision that has been made. Other factors that will be recorded include patient demographic factors (age, sex, education) and medical characteristics. See Table 2 for secondary outcomes.

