### Participants

The inclusion criteria for participants are based on the Dutch guideline for CVRM. According to the guideline, the following patients are eligible for a cardiovascular risk assessment:

Especially patients

• who have high blood pressure (≥ 140 mmHg) or are already being treated for it; and/or

• who have high total cholesterol (≥ 6.5 mmol/l) or already being treated for it; and/or

• who are smokers (men ≥ 50 years, women ≥ 55 years); and/or

• who have diabetes.

In addition, patients:

• who have positive family history of CVD; and/or

• who have visible obesity.

Patients with existing cardiovascular diseases, patients at high risk based on familial hypercholesterolaemia only and patients who are primarily managed in secondary care (e.g. by cardiologists or internists or in rehabilitation programmes) will be excluded from the study. This is a clinical approach to primary prevention. We will not manipulate the process of identifying potential high-risk patients other than by informing the GPs about the inclusion criteria, to stimulate usual strategies for case finding, either by the GPs during consultation hours or by the nurses inviting high-risk patients from available patient records. To facilitate the inclusion process, the GPs and practice nurses will receive a chart stand, with the inclusion criteria which they can place on their desk.

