### Timing of measurements

Measurements will take place at three moments (see Figures 1 and 2):

- T0 (baseline): The patients will receive the first questionnaire from their GP or practice nurse at the time they are invited to enrol in the study. The nurse will send a postage-paid postcard with the patient number to the researchers at Maastricht University (UM). Before a patient visits the practice for the first consultation, he/she will complete the first questionnaire and an informed consent form. After each consultation, the nurse will record on a standardised form some patient characteristics like age, sex, blood pressure, cholesterol level, glucose level, height, weight and the occurrence of CVD in the family (yes or no).

- T1 (12 weeks): A second questionnaire and the pedometer will be sent to the patient's home address.

- T2 (52 weeks): The final questionnaire will be sent to the patient's home address. The nurses will be asked to record data regarding the biological parameters (cholesterol level, blood pressure, glucose, diabetes yes/no) from the most recent patient contact.

All the questionnaires, the informed consent form and a form to record the number of steps that were made are to be sent to the researchers in a postage-paid envelope after completion. Materials (questionnaires, informed consent form, recording forms for nurses, initial postcard) will carry a unique patient number.

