### Data analysis

Since it is not possible to restrict our study to one primary outcome for all patients beforehand, the study will examine 6 different lifestyle changes: smoking, physical exercise, fat intake, fruit, vegetables and alcohol.

To assess the difference in primary outcomes between the arms, the arms will first be compared in terms of changes in the specific lifestyle issues, independent of the targets chosen by the intervention patients. We will use a T test for continuing variables and a χ^2 ^test for dichotomous variables.

A second analysis of primary outcomes is a multilevel regression analysis (using SPSS and MLwin), which uses adherence to the primary outcomes of lifestyle change as the dependent variables and group allocation and pre-intervention scores as independent variables. Additional independent variables will be included in the model, such as patient characteristics (age, sex, anxiety and risk of CVD). Additional regression analyses will focus on the effect at T2.

The third analysis involves constructing a simple standardised overall adherence score for the six lifestyle items, which expresses to what extent, on average, patients achieved the behaviour change goals of the national recommendations for a healthy lifestyle. The score of the intervention group will be compared with that of the control group.

Finally, the reduction in the 10-year risk of CVD will be analysed for differences between the two arms. The risk of CVD will be analysed with a multilevel regression analysis, which uses the risk at 52 weeks as the dependent variable and group allocation and pre-intervention risk as independent variables.

The secondary outcomes will also be analysed for the differences between the arms, using a T test for continuing variables and a χ^2 ^test for dichotomous variables. We also intend to use a multilevel regression analysis (using MLwin) which uses e.g. self-efficacy and attitudes at T1 as the dependent variables and group allocation and pre-intervention scores as independent variables. Additional independent variables, such as patient characteristics (age, gender, risk of CVD and socio-economic status), will also be included in the model. Additional regression analyses will focus on the effect at T2. Further analyses for subgroups of patients are also possible.

In addition, we will describe the personal targets of the patients in the intervention arm, which will be recorded by the nurses.

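### Ten-year CVD risk comes from two instruments but is analysed in one model without a diabetes term, which costs precision if the scales differ; the 52-week instrument for newly diagnosed diabetes is also not fixed

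*Protocol article*

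**What the plan says.** All references are to the protocol article.

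- **Instrument without diabetes.** Under Variables and measurements (Effect evaluation), "the absolute risk of cardiovascular events in 10 years will be calculated using the risk table from the Dutch guideline for CVRM". Under (1) Risk assessment, "The risk table is derived form the European Score risk table", with adaptation to the Dutch situation.
- **Instrument with diabetes.** Variables and measurements: "For patients with diabetes, the UK PDS risk engine will be used". Under (1) Risk assessment the tool is slightly different: "The cardiovascular risk of patients with diabetes will be estimated with a table derived from the UKPDS risk engine".
- **Eligibility.** The Participants section admits patients "who have diabetes", on that ground alone. No expected share is given.
- **Analysis.** Data analysis (Effect evaluation) plans one multilevel regression, "which uses the risk at 52 weeks as the dependent variable and group allocation and pre-intervention risk as independent variables". For the lifestyle and secondary outcomes the same section adds patient characteristics as covariates. For risk it names none.
- **Table 1.** One row covers 10-year risk, "based on patient's sex, age, blood pressure, cholesterol and smoking behaviour". Diabetes is not mentioned, although the text below the tables lists it among the determinants.
- **52 weeks.** Nurses record "cholesterol level, blood pressure, glucose, diabetes yes/no" from the latest contact, and risk is estimated again from the medical records.
- **Use and status.** The base-case cost-effectiveness ratio rests on the estimated reduction in events from the 52-week data. The Discussion says cardiovascular risk is not the primary outcome, although Table 1 lists it under that heading.

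**The concern.** One regression line is fitted to scores from two instruments. Nothing in the article shows that they share a scale, or that baseline predicts follow-up with the same intercept and slope on each. If they do not, patients with diabetes lie systematically off the common line, and the arm contrast absorbs any difference between arms in the proportion of such patients. Randomisation balances that proportion on average. But whole practices are randomised, only 10 per arm, so the realised imbalance can be appreciable.

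A smaller question concerns patients diagnosed during the year. Diabetes status is recorded again at 52 weeks and status decides the instrument, yet no sentence says which instrument then applies.

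At stake are the precision of the 52-week risk contrast, the meaning of a pooled mean score, and the risk input of the economic evaluation.

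**Working it through.** The plan has no figure to reproduce here. It gives no diabetes share, incidence, SD of risk or difference between instruments, and the sample size is based on adherence. The numbers of practices (20, 10 per arm) and patients (300 per arm at 52 weeks) are the plan's. Every other input below is an assumption.

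**1. How an imbalance reaches the contrast.** Let Δp be the difference between arms in diabetes share, and δ the average distance, in risk points, of patients with diabetes from the common regression line. The contrast then moves by about Δp × δ. Randomisation gives E(Δp) = 0, so there is no bias in expectation. The added SD is SD(Δp) × |δ|.

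**2. Size of Δp.** Assume a 30% share with between-practice SD s, and ignore the regional stratification:

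SD(Δp) = √[2 × (s²/10 + 0.3 × 0.7/300)]

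- s = 0.10: √[2 × (0.00100 + 0.00070)] = √0.0034 = 0.058
- s = 0.15: √[2 × (0.00225 + 0.00070)] = √0.0059 = 0.077

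An imbalance of 6 to 8 percentage points is thus one standard deviation. Each risk point of δ adds an SD of about 0.06 to 0.08 points to the contrast.

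**3. Gain from a diabetes term.** Two sets of simulations used 20 practices of 30 patients, with the diabetes scale equal to or wider than the other. The first had 1,500 replicates and a baseline slope of 0.7. Absolute SDs depend on assumed variances, so read the ratios.

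| Diabetes scale | SD without → with diabetes terms, first set | Second set |
|---|---|---|
| Equal | 0.120 → 0.120 | no loss |
| 2 times wider | 0.189 → 0.171 | 0.195 → 0.176 |
| 3 times wider | 0.266 → 0.222 | 0.264 → 0.224 |

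The reductions in the second set are 1 − 0.176/0.195 = 10% and 1 − 0.224/0.264 = 15%; the first set gives 10% and 17%. Almost all of the gain came from the main effect of diabetes, and little from its interaction with baseline risk.

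**4. New diabetes during the year.** Suppose a newly diagnosed patient does change instrument, and the change moves the score by g points. The shift in the contrast is (incidence in intervention arm − incidence in control arm) × g.

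| Incidence, intervention vs control | g = 5 | g = 10 | g = 20 |
|---|---|---|---|
| 2% vs 2% | 0 | 0 | 0 |
| 4% vs 2% | 0.1 | 0.2 | 0.4 |
| 5% vs 2% | 0.15 | 0.3 | 0.6 |

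With 2% in both arms, each arm's mean moves by 0.1, 0.2 or 0.4 points, but this cancels in the contrast. What remains is noise: g × √(0.02 × 0.98) = 0.7, 1.4 or 2.8 points of added SD per patient.

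A simulation of the pooled regression (300 per arm, 25% with diabetes at baseline, no true effect, no clustering) agrees. With equal incidence the mean arm effect was −0.007, −0.001 and 0.004. With 4% against 2% it was 0.07, 0.16 and 0.30. The latter are close to 0.75 × 0.02 × g = 0.075, 0.15 and 0.30, since only the 75% without diabetes at baseline can convert.

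**The case against.** The strongest defence has four parts.

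- **Pooling does not bias the comparison.** This stands. A reader might infer that mixing instruments distorts the treatment effect; steps 1 and 4 show that it does not in expectation. The issue is efficiency.
- **The instrument switch is not stated.** This also stands. A reader might infer that newly diagnosed patients change instrument, so that part of the observed risk change is an artefact of scale. That follows only from reading the diabetes rule and the 52-week diabetes record literally together; no sentence says so, and a fuller document could settle it. It would concern only patients whose status changes, and part of their rise may be real added risk.
- **Unequal detection between arms is not shown.** Nurses in both arms are trained on the same guideline and estimate risk. Against this, the intervention brings two consultations and a call, and glucose is among the items recorded after consultations, so more detection in that arm is possible. The document does not establish it.
- **Both tools are described as giving absolute 10-year risk, and risk is not the primary outcome.** The shared description does not show a shared scale, and how far they differ cannot be learned from the article. The lower status limits the weight of the point. It does not remove it, because Table 1 lists risk as primary and the economic base case uses it.

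The Table 1 omission can fairly be called shorthand, since the text supplies the full definition. It is an editorial correction.

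**Conclusion.** The point holds as one of precision and clarity. Two instruments feed one outcome, and the stated model has no term to separate them. If the scales differ, chance imbalance in diabetes share across 20 practices adds noise that one available covariate would remove: roughly 10% to 15% off the SD of the arm estimate if the diabetes scale is two to three times wider, nothing if the scales are equal. These figures rest wholly on assumed scale ratios, shares and variances.

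The document does not support a claim of bias from pooling, or a claim that the planned risk change is partly a scale artefact. For patients newly diagnosed with diabetes it supports only this: the 52-week instrument is not fixed, and if the instrument did change, the contrast would be biased only where new diagnoses differ between arms. The change is worth making because it is nearly free, not because the present analysis would be invalid.

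**What to change.** - **Main change.** Add baseline diabetes status, which identifies the instrument, to the multilevel risk model under Data analysis and to the risk input of the base-case cost-effectiveness ratio. Its interaction with pre-intervention risk is optional.
- **New diabetes.** State which instrument is used at 52 weeks for a patient diagnosed during the year. Add a sensitivity analysis that keeps the baseline instrument at both time points, or is limited to patients with unchanged status, and report new diabetes by arm. Either version leaves out any real added risk from new diabetes, so it should accompany the main analysis and not replace it.
- **Wording.** Align the Table 1 row with Variables and measurements by naming diabetes and both instruments. State whether the diabetes instrument is the engine or a table derived from it.

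The cost is one model term, one sensitivity analysis and a few lines of text. No new measurement is needed, because baseline status already decides the instrument. The illustrative list of baseline items under Timing of measurements does not name diabetes, however, so it should be confirmed that the status is on the recording form.
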